## Abstract

**Background:**

Pulse perfusion index (PI) reflects blood perfusion. It has been reported that PI can be used to evaluate the effect of nerve block, but currently, it is mainly focused on awake adults. In pediatric general anesthesia, it has been reported that PI can evaluate the effect of the sacral block. Still, there is a lack of relevant research on the impact of brachial plexus blocks. Our objective is to assess the prediction effects of PI on the success of supraclavicular brachial plexus block in pediatric patients under sevoflurane or propofol general anesthesia.

**Methods/design:**

This is a mono-center, parallel, 2-arm randomized superiority trial. One hundred four children aged 1 month to 12 years who undergo upper limb surgery will be enrolled in this study. According to anesthesia induction and maintenance medication, they will be divided into sevoflurane and propofol groups. The PI values of the index and little finger will be recorded on the blocked and non-blocked sides of supraclavicular brachial plexus block (SCB) in all children. The primary outcome is to assess the effects of PI on the success of supraclavicular brachial plexus block in pediatric patients under sevoflurane or propofol general anesthesia. The secondary outcome includes mean arterial blood pressure (MAP), heart rate (HR), and correlation between baseline PI and 10 min after SCB (PI ratio).

**Discussion:**

This trial will provide evidence on the changes in PI after SCB in sevoflurane or propofol anesthesia in children. SCB may lead to changes in PI values under sevoflurane or propofol anesthesia. After the children wake up at the end of the surgery, the changes in PI values on the block side and non-block side may be helpful to judge the effect of nerve block when excluding the influence of anesthetics.

**Trial registration:**

ClinicalTrials.gov NCT04216823. Registered on 15 July 2020.

## Introduction

Fractures are common diseases in the growth and development of children [1]. Naranje SM et al. reported that the incidence of fractures is 180/1000 throughout childhood and adolescence, and 17.8% of all fractures is forearm fracture. Finger and wrist fractures are the second and third most common fractures [2]. An epidemiological analysis of 1067 child fractures in Switzerland indicated that 76% of the fractures were upper limb fractures. Among them, 86% (694) were treated with plaster fixation or closed reduction, 11% (92) were treated with fast reduction nails or elastic stable intramedullary nails, and 3% required open reduction and internal fixation [3]. In addition, fractures cause movement limitation and obvious pain. Fully adequate anesthesia and analgesia are essential parts of fracture treatment.

Brachial plexus block (BCB) has a long history of being used for anesthesia and postoperative analgesia in upper limb surgery [4, 5]. There are four frequently used approaches for brachial plexus block: interscalene block, supraclavicular block, subclavian block, and axillary block [6, 7]. Traditionally, the supraclavicular block is seldom used because it is prone to pneumothorax, phrenic nerve block, intravascular injection, and Horner syndrome [8]. In recent years, with the development of real-time ultrasound-guided nerve blocks, anesthesiologists with extensive experience in ultrasound-guided nerve blocks can safely perform supraclavicular brachial plexus block in children under general anesthesia [9, 10]. Most regional anesthesia is performed under general anesthesia because uncooperative children may increase the risk of additional injury [11]. Walker BJ et al. analyzed the data of 100,000 children with regional block from more than 20 hospitals. They believed that regional anesthesia under general anesthesia was safe, and none of the children had permanent nerve damage, which was consistent with the risk of nerve block in awake adult patients [12]. However, evaluating the effect of nerve block usually requires the patient's cooperation, and it is unsuitable for patients under sedation and general anesthesia. In recent years, some scholars have discovered new objective indicators for estimating the effect of nerve block [13]. The pulse perfusion index (PI) is an indicator that reflects blood perfusion [14]. It is the pulsating blood flow to non-pulsating blood flow in peripheral tissues measured by a special pulse oximeter and is regulated by autonomic nerves. After a successful nerve block, the blocked autonomic nerve caused local vascular dilatation. It increases skin temperature, as well as increases regional perfusion, which will lead to changes in PI value [15].

Currently, studies found that PI can be used to evaluate the effect of nerve block primarily focused on awake adults [16, 17]. Xu Z reported that PI provides an earlier and more sensitive indicator to assess the onset of caudal block under ketamine anesthesia [18]. Still, there is a lack of relevant research on the effect of peripheral nerve block in children. The supraclavicular brachial plexus block (SCB) can be used for surgical anesthesia and analgesia of the upper arm, elbow, forearm, wrist, and hand below the shoulder joint. Therefore, the aim of this study is to evaluate the effect of PI on predicting the success of SCB in children under general anesthesia with sevoflurane and propofol.

## Methods and design

### Aim of the study

This study aims to describe the role of PI in evaluating the predictive effect of SCB in children under general anesthesia with sevoflurane and propofol. Meanwhile, whether PI could predict the success of SCB by reflecting the impact of ulnar nerve block.

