### Sample size

According to literature reports [15], the probability of ulnar nerve insufficiency is less than 20%; the sample size is calculated: As shown in Table 1, the preliminary estimated sample size is 47 cases, and the withdrawal rate is assumed to be 10%. The calculation is 52 cases per group, so 104 children will be included in this experiment.

**Table 1 Tab1:** Sample size estimation results

		Type I Error- Alpha			
		0.20	0.10	0.05	0.01
Type II Error -Beta	0.20	16 + 4	23 + 6	30 + 8	46 + 12
	0.10	21 + 6	29 + 8	**37 + 10**	54 + 14
	0.05	26 + 7	35 + 9	43 + 11	62 + 16
	0.01	37 + 10	47 + 12	57 + 15	78 + 20

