### Randomization

Prior to the commencement of the clinical study, the investigator will discuss the trial with the children and children’s guardian, including the research nature, the purpose of the study, possible benefits and risks, and the rights and obligations of the subject. The guardian signed the consent form, and the children who meet the eligibility criteria were randomly assigned to the sevoflurane group (SEV group) or propofol group (PRO group) in a 1:1 allocation. A computer-generated randomization schedule will allocate subjects. Allocations were maintained on a secure website accessed just before the procedure begin.

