### Block effect evaluation

Complete block: There is no significant fluctuation of the HR, BP, and RR during the operation (heart rate and blood pressure increased by less than 10% compared with the baseline value, and respiratory rate increased by less than 20%). Partial block: When a non-single nerve innervates the surgical site, there is a specific innervated area that causes HR, BP, and RR fluctuations (HR, BP increase ≥ 10% from the baseline value, RR increase ≥ 20%), while there is no significant fluctuation in operation in other innervated area. Block failure: Operation in any innervated area caused substantial changes in HR, BP, and RR. For partial block and failure of block, a single dose of sufentanil (0.01 μg/kg) and a pump of 0.1–0.2 μg/kg/min remifentanil for supplementary analgesia.

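### The second aim and the sample size rest on ulnar nerve block, but the block is graded only by reaction at the operated site, so ulnar status can be assessed in only part of the sample

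*Protocol article*

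**What the plan says.** Four parts of the protocol article bear on this.

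- **Aim of the study.** The first sentence concerns PI and the effect of the supraclavicular block (SCB) in general. A second sentence adds an ulnar question: "whether PI could predict the success of SCB by reflecting the impact of ulnar nerve block".
- **Sample size.** The only rate given is ulnar: citing the literature, it states that "the probability of ulnar nerve insufficiency is less than 20"%. From Table 1, "the preliminary estimated sample size is 47 cases" (bold cell 37 + 10), and after a 10% withdrawal allowance: "The calculation is 52 cases per group, so 104 children will be included in this experiment".
- **Eligibility and exclusion criteria.** Any elective operation on the upper extremity qualifies. The Introduction lists upper arm, elbow, forearm, wrist and hand as areas the block can serve.
- **Block effect evaluation.** Complete block means: "There is no significant fluctuation of the HR, BP, and RR during the operation". Partial block applies where more than one nerve supplies the surgical site and "there is a specific innervated area that causes HR, BP, and RR fluctuations", while the other areas stay quiet. Failure is a reaction wherever the surgeon operates.

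Design of the study relates PI to these three classes. The article describes no nerve-by-nerve or ulnar assessment.

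**The concern.** The classification registers a nerve only if surgery stimulates the area it supplies. A child whose ulnar nerve was missed, whose other nerves are blocked, and whose operation lies outside ulnar territory has nothing to react to and meets the definition of complete block. Had the same child been operated on in ulnar territory, the grade would be partial or failed.

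Two consequences follow. Some ulnar-spared children enter the success class, so any link between PI and ulnar block is diluted by an amount that depends on the mix of operations. And the rate used for sizing describes a condition (ulnar insufficiency) that is not the one the trial observes (reaction at the surgical site).

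**Working it through.** **1. The plan's own figure.** Table 1 can be reproduced as a one-sample ROC calculation. The article names neither a method nor an AUC, so AUC 0.80 against 0.50 and two-sided testing are inferred from the fit. Let S be the smaller group (insufficient) and L = 4S the larger, which corresponds to 20% insufficiency.

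- Variance: V(A) = (A/(2−A) − A²)/S + (2A²/(1+A) − A²)/L
- With L = 4S: S·V(0.5) = 0.08333 × 1.25 = 0.10417, root 0.3227; S·V(0.8) = 0.02667 + 0.07111/4 = 0.04444, root 0.2108
- S = (1.960 × 0.3227 + 1.282 × 0.2108)² / 0.30² = 9.06; L = 36.22
- Rounded up: 10 + 37 = 47, the bold cell. The same formula gives all 16 cells.
- Withdrawal: 47 × 1.1 = 51.7, so 52 per group and 104 in total.

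On this reading the sizing needs about 10 ulnar-insufficient children per group to be recognised as unsuccessful.

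**2. What the classification can recognise.** Let p be the ulnar insufficiency rate and f the share of ulnar-spared children operated on in ulnar territory. The article gives no case mix, so the f values are assumptions. Assume also that no other nerve fails and that every stimulated unblocked nerve produces a reaction.

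- Ulnar-spared per group: 47p. At p = 0.20, the upper end of the stated range, this is 9.4, leaving 37.6 with the ulnar nerve blocked.
- Graded partial or failed: 9.4f. Graded complete: 9.4(1 − f).
- A test that reads ulnar status perfectly calls 37.6 children successes. Its apparent sensitivity for success is at most 37.6 / (37.6 + 9.4(1 − f)), in general (1 − p)/(1 − pf).

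| f | graded partial/failed (p = 0.20) | graded complete though spared | ceiling, p = 0.20 | ceiling, p = 0.10 (assumed) |
|---|---|---|---|---|
| 0.25 | 2.35 | 7.05 | 37.6/44.65 = 84% | 42.3/45.825 = 92% |
| 0.50 | 4.70 | 4.70 | 37.6/42.30 = 89% | 42.3/44.65 = 95% |
| 0.75 | 7.05 | 2.35 | 37.6/39.95 = 94% | 42.3/43.475 = 97% |

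**3. Effect on the inferred ROC sizing.** Take 10 ulnar-insufficient among 47 and let c = 10(1 − f)/(47 − 10f) be the share of the complete class that is ulnar-spared. The observed AUC is 0.80(1 − c) + 0.50c. Power is Φ[(AUC − 0.5 − 1.96√V(0.5))/√V(AUC)] with S = 10f.

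| f | recognised | c | AUC | power |
|---|---|---|---|---|
| 1 | 10 | 0 | 0.80 | 93% |
| 0.75 | 7.5 | 6% | 0.78 | 76% |
| 0.50 | 5 | 12% | 0.76 | 49% |
| 0.25 | 2.5 | 17% | 0.75 | 18% |

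These power figures are conditional on the inferred AUC as well as on f. They show the direction and do not estimate this trial's power.

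**The case against.** The main target is success of the SCB: the Introduction, the first aim, Design of the study and the primary outcome all say so, and a surgical-site standard is coherent for that. The ulnar clause is the second aim, and its endpoint is still SCB success, with ulnar block as the proposed route. The Introduction also notes that usual block testing needs a cooperative patient and does not suit general anaesthesia, so a haemodynamic surrogate is largely forced. All of this stands. It limits the point to the ulnar aim and the sizing rate.

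Stronger readings are tempting but not supported:

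- *Every ulnar-spared child is graded complete.* No. Those operated on in ulnar territory would react and be graded partial or failed.
- *The ulnar aim cannot be answered.* Too strong. The classification informs it wherever ulnar territory is operated on.
- *Little-finger PI is the designated ulnar test, and a low value in these children will be scored as an error.* Outcomes lists index and little finger together and assigns neither to a nerve. No PI cut-off or scoring rule is set, and Statistical analyses names group comparisons and logistic regression, not sensitivity. The Discussion adds that both anaesthetics raise PI, so a low little-finger value with a spared ulnar nerve cannot be taken for granted.

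A further objection is that classifying partial block already requires knowing which areas supply the site, and that subset analyses may sit in a fuller document. The first half is fair and makes the fix cheaper. The second does not remove the point, because the article states the aim, the rate and the classification explicitly and they do not match.

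**Conclusion.** The point holds in limited form. As written, children with a spared ulnar nerve who are operated on outside ulnar territory are classed as complete block. The ulnar aim can therefore be assessed in only part of the sample. The Sample size rate is also not the rate of the partial/failed class: that class loses unstimulated ulnar sparing and gains failures of other nerves, so the net direction is not known.

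The size cannot be fixed from the document. The 84%, 89% and 94% ceilings assume 20% insufficiency, no other failures, and assumed case-mix shares of 25%, 50% and 75%. Because the article says less than 20%, they mark the larger end of the loss; at an assumed 10% they become 92%, 95% and 97%. A reader might infer from the power table that the trial is underpowered. The documents do not support that, since neither the AUC nor the case mix is stated. The main analysis of surgical-site block success is not affected by the mislabelling, although its event rate remains unsupported.

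**What to change.** 1. Record for each child whether the operated area includes ulnar territory and, where the partial-block definition identifies it, which innervated area reacted.
2. Analyse little-finger PI for the ulnar question, and make the ulnar claim, only in children with ulnar-territory surgery. Treat ulnar status as not assessable in the rest.
3. State that where several nerves supply the field, a reaction may come from a non-ulnar nerve, so even this subset does not isolate ulnar status.
4. Keep the main analysis in all children and label its endpoint surgical-site block success.
5. In Sample size, state that the assumed rate is an ulnar rate used as a stand-in for the partial/failed rate.
6. If few children are assessable, report the ulnar result as descriptive.

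The cost is one more case-report-form item, some rewording, and a smaller denominator for the ulnar question. No treatment or procedure changes.

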### Design of the study

This is a parallel, 2-arm randomized superiority trial (protocol version 1.0, 05.22.2020). Tongji Hospital affiliated to Tongji Medical College of Huazhong University of Science & Technology acting as the sponsor. Pediatric upper limb surgery cases will be collected in Tongji Hospital from May 2020 to December 2022. Children were divided into propofol and sevoflurane groups by the random number table method. PI values of the index finger and little finger in the blocked and non-blocked sides will be recorded in all children. Analyzing the possible relationship of the changes in PI values with complete block, partial block, and block failure in each group. A comparative analysis of sevoflurane and propofol block cases will determine whether PI can better judge the effect of supraclavicular brachial plexus block in which general anesthesia in children. The flowchart of this study is presented in Fig. 1. The schedule of enrollment, interventions, and assessments is shown in Fig. 2.

**Fig. 1 Fig1:**
[figure not shown]
Flowchart of this study

**Fig. 2 Fig2:**
[figure not shown]
Participant timeline

### Sample size

According to literature reports [15], the probability of ulnar nerve insufficiency is less than 20%; the sample size is calculated: As shown in Table 1, the preliminary estimated sample size is 47 cases, and the withdrawal rate is assumed to be 10%. The calculation is 52 cases per group, so 104 children will be included in this experiment.

**Table 1 Tab1:** Sample size estimation results

		Type I Error- Alpha			
		0.20	0.10	0.05	0.01
Type II Error -Beta	0.20	16 + 4	23 + 6	30 + 8	46 + 12
	0.10	21 + 6	29 + 8	**37 + 10**	54 + 14
	0.05	26 + 7	35 + 9	43 + 11	62 + 16
	0.01	37 + 10	47 + 12	57 + 15	78 + 20

### Eligibility and exclusion criteria

Eligibility criteria:Age from 1 month to 12 yearsASA class I–IIElective upper extremity surgery in childrenSign the informed consent, and agree to participate

Exclusion criteria:Refusal by family membersChildren with abnormal behavior, including internalizing problems and externalizing problemsInflection at the puncture siteOther regional anesthesia contraindicationsChildren are allergic to known ingredients of experimental drugs

Withdrawal criteria:After selection, the patient is found not to meet the selection or exclusion criteria.Children experienced severe adverse reactions or exacerbations during the clinical study.

### Randomization

Prior to the commencement of the clinical study, the investigator will discuss the trial with the children and children’s guardian, including the research nature, the purpose of the study, possible benefits and risks, and the rights and obligations of the subject. The guardian signed the consent form, and the children who meet the eligibility criteria were randomly assigned to the sevoflurane group (SEV group) or propofol group (PRO group) in a 1:1 allocation. A computer-generated randomization schedule will allocate subjects. Allocations were maintained on a secure website accessed just before the procedure begin.

### Implementation

After screening the child as a qualified subject and giving informed consent, a sealed opaque envelope containing a card with the computer-generated assignment number (1 = SEV group, 2 = PRO group) will be opened by an anesthesia assistant who was not involved in the study. Anesthesiologists unblinded to the grouping of subjects are responsible for anesthesia management and nerve block according to the predetermined anesthesia.

### Interventions

The children will be given a slow intravenous bolus of 0.1 mg/kg midazolam for sedation during the waiting period. After entering the operating room, routinely monitor the electrocardiogram (ECG), heart rate (HR), blood pressure (BP), respiration rate (RR), and pulse oxygen saturation (S_P_O_2_). SEV group: Inhalation of sevoflurane (5%-8%) for induction of anesthesia, sufentanil 0.2 μg/kg, penehyclidine hydrochloride 0.01mg/kg, dexamethasone 0.1 mg/kg. Place the laryngeal mask, and maintain anesthesia with 1.0 MAC value of sevoflurane + 50% oxygen. PRO group: propofol 3 mg/kg, sufentanil 0.2 μg/kg, penehyclidine hydrochloride 0.01 mg/kg, dexamethasone 0.1 mg/kg are given for anesthesia induction. Place the laryngeal mask, and propofol 3 mg/kg/h is given for anesthesia maintenance. Then, all children will be placed supine with their heads tilted to the opposite side. Under ultrasound guidance, an experienced anesthesiologist will use an in-plane needle to block the supraclavicular nerve and give 0.25% ropivacaine 0.4 ml/kg.

### Outcomes

#### Primary outcome

The primary outcome is to assess the effects of PI on the success of supraclavicular brachial plexus block in pediatric patients under sevoflurane or propofol general anesthesia. PI values of the index finger and little finger will be recorded before induction of general anesthesia in the operating room, immediately after laryngeal mask placement, 5 min, 10 min, 15 min after SCB, immediately after surgery, after removal of laryngeal mask when the child is awake and in PACU. Record the dosages of opioids and vasoactive drugs during the operation. Evaluate the complications and recovery quality in children. (1) Assessment of restlessness and delirium during the recovery period and 30 min in PACU. (2) Postoperative pain score. Postoperative complications: nausea and vomiting, neurological dysfunction, Horner syndrome, respiratory depression, etc.

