#### Secondary outcomes

The secondary outcome includes mean arterial blood pressure (MAP), heart rate (HR), and PI ratio (correlation between baseline PI and 10min after SCB). The age, gender, ASA classification, BMI, anesthesia time, operation time, anesthesia recovery time, duration of stay in PACU, and duration of postoperative hospital stay will be recorded.

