### Data collection and management

Record the PI values of the index finger and little finger on blocked and non-blocked sides in all children. Data collection and completion will be carried out by two research assistants blinded to the grouping of subjects. The clinical trial supervisors will periodically review the quality of data entry to ensure the authenticity and reliability of the program. This data supervision committee has no conflict of interest in the study. All information related to the study will be stored securely.

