The pediatric nerve block is mainly performed under sedation or general anesthesia [21, 22]. Sevoflurane and propofol are commonly used for induction and maintenance of general anesthesia in children [23, 24], but both have a vasodilator effect. Sebastiani Anne found that PI values of the two limbs were not significantly different but relatively higher than baseline values after 25 min of intermuscular sulcus block and sevoflurane inhaled for maintenance. Sevoflurane is considered to increase PI value by increasing blood flow of the muscle tissue on the unblocked side, and the PI value of the blocked side does not increase, which means that vasodilatation has reached the maximum after nerve block [19]. Park SG et al. found that the PI value increased after propofol anesthesia induction and sevoflurane anesthesia maintenance in patients without regional block [25]. Both propofol and sevoflurane general anesthesia affects the PI value. There is still no study about PI changes after brachial plexus nerve block after sevoflurane or propofol anesthesia induction in children. We speculate that the changes of PI after brachial plexus block may exist in different periods after the administration of sevoflurane or propofol. For example, when the vasodilator effect of propofol reaches its peak, the PI may have increased to the highest value. At this time, PI may not increase further after nerve block. However, PI values will change differently following the metabolism of anesthetics on the blocked and non-blocked sides. Moreover, the surgery for upper limb fractures could always be completed in about 1 h in children. And anesthesia and analgesia effect last 6–8 h after nerve block with ropivacaine. We will monitor the PI values of both sides after nerve block at the beginning and the end of the surgery. The influence of general anesthetics on PI values will be excluded after children wake up.

In conclusion, we intend to evaluate the prediction effect of PI on supraclavicular brachial plexus block after the induction of general anesthesia with sevoflurane or propofol in children, which could be used as a clue to evaluating the requirements of postoperative analgesics in children.

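### The PI schedule has no reading just before the block under maintenance anaesthesia, so single-limb measures such as the PI ratio mix the block effect with the shift from induction to maintenance

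*Protocol article*

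**What the plan says.** All places are in the protocol article.

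- **Primary outcome.** The first PI reading is "recorded before induction of general anesthesia in the operating room". The next are "immediately after laryngeal mask placement, 5 min, 10 min, 15 min after SCB, immediately after surgery". The last are after mask removal when the child is awake, and in PACU.
- **Interventions.** Induction uses 5%-8% sevoflurane or a 3 mg/kg propofol bolus. The sevoflurane arm then continues: "Place the laryngeal mask, and maintain anesthesia with 1.0 MAC value of sevoflurane + 50% oxygen". The propofol arm continues: "Place the laryngeal mask, and propofol 3 mg/kg/h is given for anesthesia maintenance". Positioning and the ultrasound-guided block follow. No interval from mask to block is given.
- **Secondary outcomes.** One endpoint is the "PI ratio (correlation between baseline PI and 10min after SCB". It does not say which reading is the baseline and makes no reference to the other limb.
- **Data collection and management.** "Record the PI values of the index finger and little finger on blocked and non-blocked sides in all children".
- **Discussion.** Both anaesthetics are said to affect PI, and the authors expect that "when the vasodilator effect of propofol reaches its peak, the PI may have increased to the highest value". They also state: "We will monitor the PI values of both sides after nerve block at the beginning and the end of the surgery".
- **Block effect evaluation.** Complete, partial and failed block are judged from heart rate, blood pressure and respiratory rate during the operation. Partial and failed blocks then receive supplementary opioids.

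**The concern.** The trial asks whether PI reveals a successful block in an anaesthetised child, and under which of two anaesthetics it does so better. Both questions need the PI change caused by the block. The schedule brackets the block with a reading at the induction level of the drug and a reading at the maintenance level, so the bracket also contains a change in anaesthetic vasodilation. The drugs and regimens differ by arm, so this extra component may differ by arm too. It would then enter the between-arm comparison as well as the accuracy within each arm.

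A smaller second issue lies at the other end. The 5, 10 and 15 min readings are timed from the block alone, while the Discussion speaks of monitoring at the start of surgery, a time point that the outcome list does not contain. Block success is judged during the operation, so a reading taken after incision would no longer be a prediction. It could also follow opioids given only to children whose block was not complete.

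**Working it through.** **Step 1. Order of events (Interventions) against the listed readings (Primary outcome).**

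| Event | PI reading listed |
|---|---|
| Before induction | yes |
| Induction, mask placed | yes, immediately after the mask |
| Maintenance started, child positioned | none |
| Immediately before injection | none |
| 5, 10, 15 min after the block | yes |
| Start of surgery / incision | none listed, although the Discussion mentions the beginning of surgery |
| End of surgery, awake, PACU | yes |

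**Step 2. What each available contrast contains.**

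- Blocked side, mask reading to 10 min: block effect + shift from induction to maintenance.
- Blocked side, pre-induction reading to 10 min: block effect + the whole anaesthetic effect.
- Non-blocked side over the same interval: the anaesthetic shift without the block.
- Blocked minus non-blocked change from the mask reading: block effect, with everything common to both limbs removed. What remains is anything specific to one limb or not additive, such as a ceiling on vasodilatation.

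The PI ratio is of the first or second kind, depending on an unstated baseline. I read it as the 10-min value divided by baseline, although the text calls it a correlation.

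**Step 3. Illustration of size.** The only limit in the document is the 10-min PI ratio of 1.4, quoted in the Discussion from a study in awake adults. Two inputs are my assumptions and are not in the document: a true ratio of 1.8 for a successful block (1.0 for a failed one), and an anaesthetic drift of 20-30% between mask placement and 10 min.

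Observed ratio = true ratio × (1 + drift).

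- Successful block, effect falling 20%: 1.8 × 0.80 = 1.44, above 1.4.
- Successful block, effect falling 30%: 1.8 × 0.70 = 1.26, below 1.4.
- Break-even: 1.4 / 1.8 = 0.78, a fall of about 22%.
- Failed block, effect rising 20% to 30%: 1.0 × 1.20 = 1.2 to 1.0 × 1.30 = 1.3, both below 1.4.
- Rise needed to lift a failed block to the limit: 1.4 / 1.0 − 1 = 40%.

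**Step 4. The same drift with the other hand as control.** If the drift acts equally on both limbs, the blocked ratio divided by the non-blocked ratio is (1.8 × 0.70) / (1.0 × 0.70) = 1.8. The common drift cancels. For proportional drift, the side contrast must be formed on ratios (or logs) to cancel exactly. A plain difference in change cancels an additive drift.

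**The case against.** The strongest reply is that the design already has a control. Both hands are measured in every child, and the non-blocked hand passes through the same change of anaesthetic at the same times. A reader might infer from the missing reading that the block effect cannot be separated from the anaesthetic shift at all. The document does not support that: Step 4 shows that a shift common to both limbs is removed without any extra reading. This part of the objection stands. It does not rescue the PI ratio, which is stated without side adjustment.

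A related argument would dismiss the side contrast because of the ceiling effect in the Discussion, where a cited study found that under sevoflurane PI rose only on the unblocked side, the blocked limb being already fully dilated. That limits the side contrast, but an extra pre-block reading does not cure it either. A limb near its maximum cannot rise further from any baseline.

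Three further points stand in whole or in part.

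- The illustration rests on assumed values and on an adult limit that this protocol does not adopt. It shows missed successes at larger falls and no false successes.
- Overlap of the 5-15 min readings with surgery is unverified, because no block-to-incision time is given. Nor does the document say that the response to surgery lowers PI.
- The participant timeline (Fig. 2) is not shown and may list further time points, and clock times may sit on the case report form. If so, the outcome section needs aligning with them.

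Finally, the effect of the anaesthetics on PI is part of the research question, and the awake readings are meant to exclude it. Those readings come after surgery, so they do not supply a pre-block value for judging the block at 10 min.

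**Conclusion.** The point holds in a limited form. The listed schedule has no PI value immediately before the block with maintenance running. Single-limb measures, the PI ratio among them, therefore combine the block effect with an anaesthetic shift that the authors themselves expect and that may differ by arm. The side contrast removes only the part common to both limbs, and the article names no endpoint built on it.

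The size cannot be derived from the document. On the assumed true ratio of 1.8, a success is missed against the 1.4 limit only if the anaesthetic component falls by more than about 22%. At a 20-30% rise no failed block is read as a success.

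Two stronger readings should be avoided: that the PI data cannot isolate the block effect, and that the post-block readings are contaminated by surgery. The first overlooks the non-blocked hand. The second needs a block-to-incision time that is not given. What can be said is that the outcome list and the Discussion disagree about a start-of-surgery reading. This is a worthwhile, inexpensive improvement and not a flaw that invalidates the design.

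**What to change.** 1. Add one PI reading on all four fingers immediately before local anaesthetic injection, with maintenance running.
2. Name that reading as the baseline for the PI ratio and for every within-finger change. Keep the mask-placement reading to describe the anaesthetic effect.
3. Report the blocked-minus-non-blocked difference in change alongside the single-limb measure, on the log scale where ratios are used.
4. Reconcile the outcome list with the Discussion on PI at the start of surgery, and align both with Fig. 2.
5. Record the clock times of injection and incision. Use only readings taken before incision for prediction, and flag any later 10- or 15-min reading.

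**Cost.** One extra reading per child from a monitor already in use, and two clock times. Some 10- or 15-min readings may leave the predictive analysis if surgery starts early. The new baseline reduces the anaesthetic component but does not abolish it: drift that continues after injection, and the ceiling on vasodilatation, remain, which is why the side contrast should be reported with it. Because the value cannot be reconstructed in analysis, the reading can only help children measured after the change is made.
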